### Primary outcome

The CONNECT Program target, psychological flexibility, is the primary outcome and will be measured with the Acceptance and Action Questionnaire-II [47] (7-item self-report). Scores range from 7 to 49, with lower scores indicating greater psychological flexibility. Psychological flexibility is a core target of ACT and has been found to function as a transdiagnostic treatment process of change in psychotherapy [48]. Psychological flexibility is selected as the primary outcome in this trial because evidence shows that psychological inflexibility is strongly correlated with anxiety (r = 0.66, p < .001) and depression (r = 0.70, p < .001) in older adults [49], and facets of flexibility such as openness and awareness demonstrate medium-to-large associations with these symptoms [50]. Moreover, interventions enhancing flexibility, including mindfulness-based CBT (g = 0.55 for depression; g = 0.58 for anxiety) [51] and ACT, have been shown to reduce psychopathology and improve quality of life in older populations [52].

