### Sustainability of The CONNECT program

Sustainability is defined as the extent to which a newly implemented treatment is maintained or institutionalized within a service setting’s ongoing, stable operations [63]. Data will be collected through a post-program survey that includes Likert-scale and open-ended questions (with items developed based on [63]). In addition, a weekly facilitator check-in questionnaire will track dropout, attendance, and participant-reported reasons for not attending or discontinuing.

A detailed overview of the assessment schedule by timepoint and study week is provided in Table 1.

**Table 1 pone.0336031.t001:** Schedule for assessment administration.

	TRIAL PERIOD						
	Enrollment		Post-randomization				6-month follow-up
Timepoint	*−1*	0	*T1*	*T2*	*T3*	*T4*	*T5*
Timing	*Week *(−4)	Week 0	*Week 1 -Week 6*	*Week 6*	*Week 7 -Week 12*	*Week 12*	*Week 30–36*
Sociodemographics		X^1,2^					
Psychological flexibility (Acceptance and Action Scale; [47]) Acceptance and Commitment Scale		X^1,2^		X^1,2^		X^2^	X^1,2^
DeJong Gierveld Loneliness Scale [53]		X^1,2^		X^1,2^		X^2^	X^1,2^
Social Isolation (PROMIS Social Isolation 8a; [55]		X^1,2^		X^1,2^		X^2^	X^1,2^
Emotional Support (PROMIS Emotional Support; [55])		X^1,2^		X^1,2^		X^2^	X^1,2^
Anxiety (PROMIS Anxiety Short Form 4a; [56])		X^1,2^		X^1,2^		X^2^	X^1,2^
Depression (PROMIS Depression Short Form 4a; [56])		X^1,2^		X^1,2^		X^2^	X^1,2^
Mental Health Literacy (Brief Mental Health Literacy Scale; [61]		X^1,2^		X^1,2^		X^2^	X^1,2^
Group Session Scale [65]			X³		X³		
Intervention Delivery Type (Adapted from [64]				X^1^		X^2^	
Intervention Content (Adapted from [64]				X^1^		X^2^	
Individual Qualitative Exit-Interview				X^1^		X^2^	
Implementation Survey (Likert-scale and open-ended items, per [63].)				X^1^		X^2^	
Weekly Facilitator Check-in Questionnaire			X³		X³		

X¹ - Participants who received The CONNECT Program first, X² - Participants who received The CONNECT Program second (after waitlist), X³ - Weekly administration during the CONNECT Program sessions only; not completed during control condition.

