### Assignment of interventions

Randomization will be conducted by a non-affiliated researcher at the Centre for Healthcare Innovation (CHI) using a secure computerized tool. We are using restricted randomization to keep group sizes balanced within each site. Details about blocking and sequence structure are recorded separately and will not be shared with staff involved in recruitment or group assignment prior to randomization. Each participant will be assigned a unique ID and randomized into one of two sequences: The CONNECT Program first or Community Programming as Usual first. Participants will be randomized prior to enrollment. The research coordinator will be aware of group assignment after randomization to manage scheduling and follow-up; however, outcome assessor and outcome analysts will remain blinded and only work with de-identified data. Group assignment will not be disclosed to the outcome assessor or analysts, and all outcome data will be labeled using participant ID codes without identifying group allocation. Due to the nature of the behavioral interventions, neither participants nor facilitators will be blinded. We do not expect unblinding to be necessary for the assessor or analysts.

If participants are unable to self-administer via a secure link then measures will be administered verbally by a trained research assistant via telephone or university-managed Zoom and responses input on the behalf of a participant. To support data quality, assessors will be trained in standardized procedures, and data will be entered directly into REDCap, which includes built-in range checks. Duplicate entries and inconsistencies will be identified during routine data cleaning. Each participant will be assigned a unique ID number to ensure confidentiality. All data will be stored on secure University of Manitoba (UM) REDCap servers and transferred to a password-protected UM OneDrive folder in accordance with the data transfer agreement, only the research team will have access to identified data.

To promote retention, participants will receive reminders for each assessment and session, along with technical assistance where needed. In cases where participants discontinue or miss sessions, they will still be invited to complete follow-up assessments, including key outcome measures where possible.

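### The statement that outcome assessors and analysts stay blinded cannot hold for analysts or for week-12 assessors, because Table 1 collects week-12 outcomes in one sequence only

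*Protocol article*

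**What the plan says.** Under *Assignment of interventions* the protocol article states that the "outcome assessor and outcome analysts will remain blinded and only work with de-identified data". The method is coding: "all outcome data will be labeled using participant ID codes without identifying group allocation". The statement is not limited by timepoint or role, and the article does not expect that the assessor or analysts will need to be unblinded.

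The same section says openly that "neither participants nor facilitators will be blinded". It makes self-completion through a link the default and adds a fallback: "If participants are unable to self-administer via a secure link then measures will be administered verbally by a trained research assistant". In the fallback the assistant speaks with the participant by telephone or Zoom and enters the answers.

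Table 1 gives the assessment schedule. The row labelled "Psychological flexibility (Acceptance and Action Scale; [47]) Acceptance and Commitment Scale" is marked for both sequences at week 0, week 6 and follow-up, but at week 12 only for participants who receive CONNECT second. The six secondary outcome rows have the same pattern. The delivery-type, content, exit-interview and implementation-survey rows are marked for CONNECT-first participants at week 6 and for CONNECT-second participants at week 12.

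**The concern.** A blinding statement describes a property of the design, and readers and risk-of-bias assessors rely on it. Here the schedule ties data collection to the sequence, so coded IDs cannot hide the sequence from anyone who sees which records exist. The person who administers a week-12 outcome scale learns the sequence from the fact that it is due.

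The primary outcome is a seven-item self-report. Knowledge of the sequence by the person reading the items aloud could influence answers, and knowledge of it by analysts could influence choices made with the data in view. At stake is whether the trial can claim blinded outcome assessment and analysis. The sample size is not affected.

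**Working it through.** The article gives no figure for blinding. Its one figure that can be recomputed is the sample size: with d = 0.5, power 80% and alpha 0.05 (taken as two-sided, which is not stated), the two-sample t-test needs 63.8, so 64 per group and 128 in total. That reproduces the stated target, and nothing below depends on it.

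**Step 1. Table 1, read cell by cell**

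| Item | Week 0 | Week 6 (T2) | Week 12 (T4) | Follow-up (T5) |
|---|---|---|---|---|
| AAQ-II and six secondary scales (7 scales) | both | both | CONNECT-second only | both |
| Delivery type, content, implementation survey (3 forms) | none | CONNECT-first only | CONNECT-second only | none |
| Exit interview (per the text after Table 1, a random 40 participants) | none | CONNECT-first only | CONNECT-second only | none |

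At week 12 the count of outcome scales is 0 in one sequence and 7 in the other. At week 6 it is 7 in both.

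**Step 2. Analysts with ID codes only**

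Take 1:1 allocation (*Patient and public involvement, trial design*) and let m be the share of CONNECT-second participants with no week-12 record. Call a participant CONNECT-second if a week-12 record exists and CONNECT-first otherwise. Every CONNECT-first participant is called correctly, and a share 1 − m of the others:

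P(correct) = 0.5 + 0.5 × (1 − m)

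| m (assumed) | P(correct) |
|---|---|
| 0 | 0.5 + 0.5 × 1.0 = 100% |
| 10% | 0.5 + 0.5 × 0.9 = 95% |
| 20% | 0.5 + 0.5 × 0.8 = 90% |
| 40% | 0.5 + 0.5 × 0.6 = 80% |

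Chance is 50%. A record that is present identifies the sequence with certainty at any m. The analysis is restricted to participants who finish both stages, which should keep m low.

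**Step 3. Analysts with neutral A/B labels**

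The model compares conditions and adjusts for sequence. That alone unblinds nobody, because both variables can be coded A/B. The schedule decodes them: one label has week-12 outcomes and the other has none, so a single week-12 record reveals the meaning of the label for everyone who carries it.

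**Step 4. Assistants who administer measures verbally**

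- *Week 12:* outcomes are due only in CONNECT-second participants, so the task itself reveals the sequence.
- *Week 6:* the seven scales are due in both sequences. The assistant learns the sequence only by also handling the CONNECT-only forms, or if the participant discloses it. The article neither states nor excludes that one person does both.
- *Follow-up:* it falls 24 weeks after CONNECT ends (Fig 1 legend), so at week 6 + 24 = 30 or week 12 + 24 = 36. This reveals the sequence to someone who knows the start date.
- *Any timepoint:* an assistant talking with a participant is not working only with de-identified data.

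**The case against.** The strongest case on the other side has four parts.

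1. **Week 6 can be masked.** It is the only post-baseline point at which the two conditions are measured in parallel, and the outcome scales are scheduled identically there. The coordinator, who is openly aware of allocation, handles scheduling and follow-up, so an assessor could be kept apart from the CONNECT-only forms. This stands. A reader might infer that every participant's sequence is exposed to the assessor at week 6, or that four extra instruments mark each CONNECT-first participant. The article supports neither. Exit interviews go to 40 of 128 participants, so 128 − 40 = 88 never have one, and three CONNECT-only forms are due for all.

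2. **The main exposure is disclosed.** Participants rate their own outcomes knowing their condition, and the article says so. It nowhere claims that blinding assessors or analysts protects the self-report. This also stands. A reader might conclude that blinding is absent altogether, which goes too far.

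3. **Verbal administration is a fallback**, done by trained assessors. This stands and limits how many participants the assessor part touches. It does not help the analyst part, which covers all participants.

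4. **No bias has been measured.** This stands. A reader might want the effect in AAQ-II points, but the article gives no share of verbal assessments, no interviewer effect and no standard deviation, so no such figure can be supported.

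None of the four restores the statement for analysts or for week-12 assessors.

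**Conclusion.** The blinding statement is wrong as written. Under Table 1, analysts working with the full outcome data cannot be blinded to sequence, and neither can an assistant who administers week-12 outcomes. The part about de-identified data does not fit any verbal assessor. Masking of a verbal assessor remains possible at baseline and at week 6, in the latter case only if that person handles no CONNECT-only form and the participant does not disclose.

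The size is 100% identification of sequence by analysts with complete week-12 data, and 80% to 95% from record presence alone if 40% to 10% of the CONNECT-second records are missing. The missing shares are assumptions. The conclusion rests on reading Table 1 as printed and on the 1:1 allocation. The direction and size of any resulting bias cannot be derived from the article.

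**What to change.** - **Restate the blinding.** Replace the sentence with one saying that outcomes are self-reported by unblinded participants, that analysts and week-12 verbal assessors cannot be kept blinded under the present schedule, and that assessor masking is attempted only at baseline and week 6.
- **Lock outcomes first.** At weeks 6 and 12, complete and lock the seven outcome scales in REDCap before any CONNECT-only form or interview is opened.
- **Separate the tasks.** Have staff who already know the allocation, such as the coordinator, handle the CONNECT-only forms, so that the assistant reading the outcome scales does not see them.
- **Freeze the analysis.** Write and freeze the analysis code before the outcome data are released. This guards against data-driven choices without relying on blinding.

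The cost is a wording change, a form-order setting and some reassignment within the existing team. The trial can no longer claim fully blinded outcome assessment and analysis, and some participants have a second short contact. Recruitment is still open, so the form order can be changed for those yet to be assessed.

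Collecting week-12 outcomes in both sequences would remove this particular leak, at the price of one more assessment for about half the sample (128 / 2 = 64). It is a larger change and is not needed to make the statement accurate.

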## Materials and methods

### Patient and public involvement, trial design

Before launching the trial, a few pre-implementation studies were conducted together with the partner community organisations across three provinces (British Columbia, Manitoba, Saskatchewan) and adult participants aged 55 + . We completed one virtual focus group per province with staff from each of the partner sites to gather input on how to adapt The CONNECT Program for different provinces [41–43]. This included feedback on revising the materials to reflect local needs, choosing the best delivery format (phone or videoconferencing), and designing a training and supervision process for community-based facilitators. We also held virtual focus groups and interviews with adults aged 55+ to learn about their mental health support needs, views on The CONNECT Program and implementation preferences [44].

This study uses a randomized crossover trial design, embedded within a type 1 hybrid implementation-effectiveness framework [45]. Participants are randomly assigned in a 1:1 ratio to begin either with The CONNECT Program or with the community-based programming. After completing the first condition, they will cross over to the other condition. Two sites will begin with videoconference mode and then switch to telephone mode, while the other two will follow the opposite sequence. In this RCT the effectiveness and implementation outcomes follow a superiority framework. Recruitment is ongoing in four Canadian provinces, with site-specific recruitment periods. The recruitment started on 8 September 2025, and is ongoing, with recruitment date for both primary and secondary end point collection expected to be collected by 30 September 2026.

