### Participants, interventions, and outcomes

The trial will be conducted in community-based settings in four Canadian provinces (British Columbia, Manitoba, New Brunswick, Saskatchewan). Inclusion criteria for participants are: adults aged 55 years or older, able to speak, read, and understand English, can manage hearing or vision challenges well enough to participate in group conversations, self-reported experiences of loneliness, social isolation, and/or mental health challenges (including anxiety/depression symptoms). The exclusion criterion is: cannot communicate in English (verbal or written). Eligible facilitators include mental health professionals (e.g., social workers, psychologists, or geriatric clinicians) who are staff or volunteers of the partner organisations, as well as trained non-clinical staff or volunteers.

The CONNECT Program is a six-week, group-based telehealth intervention designed to reduce loneliness, social isolation, and co-occurring mental health symptoms (anxiety and depression) among adults aged 55 and older. Grounded in principles of ACT [35], self-compassion [36], and theories of successful aging [37,38], the program supports participants in building psychological flexibility, strengthening meaningful social connections, and engaging in values-based action. Each group meets once a week (6 weeks) for 90 minutes, either by telephone or via videoconferencing. Groups are typically 6–8 participants. Sessions follow a consistent structure, beginning with a grounding or mindfulness practice, followed by the introduction of core concepts drawn from ACT or self-compassion, group reflection, and discussion of real-life applications. Homework exercises are assigned each week, encouraging participants to practice new skills in their daily lives. These activities are supported by a structured participant workbook, which is available in both print and digital formats, depending on individual preference. The intervention was not tailored; all participants received the same materials and delivery format. The comparator condition consists of community-based programming that is already offered by participating partner organizations as part of their routine services. These programs may include group activities with a social, educational, or recreational focus, delivered by phone, videoconference, or in person. Programming varies slightly by site but reflects the standard community-based programs available to adults 55+ in each region.

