Risks of the trial are minimal but may include psychological and emotional discomfort when discussing topics like social isolation, loneliness or mental health. Facilitators monitor participants during sessions and respond to distress following a structured safety protocol. A mental health resource list is provided to all participants, and those in the control condition continue to receive service as usual.

The trial has a target recruitment of 128 participants, with 64 in each delivery group (videoconference and telephone), based on a power calculation with Cohen effect of 0.5 alpha = 0.05 and power 80%. The effect size of 0.5 is based on our pilot data and is consistent with other similar intervention studies in older adults (e.g., [66]).

Participants will be recruited through the four partnering community organizations, with local community partners overseeing outreach. Each site will run two groups per delivery mode (videoconference and phone), with approximately 32 participants recruited per site. To support both recruitment and retention, participants will receive a $25 honorarium (e-gift card or mailed) after completing each of the three assessment points baseline, post-intervention, and follow-up – for a total of $75. An additional $25 honorarium will be provided to participants who are selected at random for qualitative interviews after participating in The CONNECT Program (n = 40; 10 per site).

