Analysis of the primary and secondary outcomes will be conducted using linear mixed-effects models to account for repeated measures and the crossover design. Changes in psychological flexibility, loneliness, social isolation, emotional support, anxiety, depression, and mental health literacy will be compared between The CONNECT Program and control conditions using repeated measures analyses, adjusting for delivery sequence and baseline values. For descriptive comparisons, both paired t-tests and repeated measures ANOVA may be used. Adverse events and participant distress will be recorded; however, harms will not be systematically evaluated. All analyses will be performed on a per-protocol basis, including only participants who complete both stages. Sensitivity analyses may include a larger sample, if applicable. Missing data will be examined for patterns; if data are missing at random, linear mixed models will be used. For key outcomes with high levels of missingness, multiple imputation or pattern-mixture models will be considered. Subgroup analyses by delivery mode and location will be conducted if sample sizes are sufficient to support interpretation.

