## Discussion

The CONNECT Program is a unique mental health support program aimed at addressing the critical service gaps faced by older adults who are experiencing social isolation, loneliness, and mental health difficulties. While our primary aim with this trial is to assess program impact on key mental health outcomes, a secondary aim is to provide real-world evidence about its implementation in different community-service settings. Also, there are a number of design and other administrative issues that should be considered. Although the hybrid trial design allows for simultaneous assessment of implementation and effectiveness outcomes, it may also complicate data interpretation. Contexts between distinct sites vary, potentially confounding attribution of outcomes to intervention.

The individual-level crossover design increases internal validity but may be affected by carryover effects between treatment periods, even with the relatively short 6-week program and no formal washout. Psychological changes may persist and influence subsequent measurements.

Furthermore, tablets and technical support will be offered, and the technological literacy of adults 55 + might influence their engagement, particularly when it comes to the delivery videoconferencing delivery. This can also affect both the implementation and effectiveness data.

Findings from this study will yield critical insights regarding the effectiveness and implementation of The CONNECT Program in a variety of community settings and delivery modalities. Given the urgent need for accessible interventions for socially isolated older adults, a successful outcome of this trial could pave the way for The CONNECT Program to be disseminated broadly as a tool to combat the epidemic of loneliness and mental health challenges in the aging population.

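### The described mixed model names neither the CONNECT group nor the randomisation site, and the sample size of 128 assumes independent participants

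*Protocol article*

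**What the plan says.** The analysis paragraph is in the protocol article under Assignment of interventions. It plans "linear mixed-effects models to account for repeated measures and the crossover design" for the primary and secondary outcomes, adjusted for delivery sequence and baseline. Location and delivery mode appear there only as subgroup analyses, conditional on sample size.

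On delivery, the section Participants, interventions, and outcomes states: "Groups are typically 6–8 participants". The paragraphs after Table 1 add: "Each site will run two groups per delivery mode (videoconference and phone), with approximately 32 participants recruited per site". The comparator is existing community programming, which may also include group activities.

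On allocation, individuals are randomised: "Participants are randomly assigned in a 1:1 ratio to begin either with The CONNECT Program or with the community-based programming". The section Assignment of interventions adds: "We are using restricted randomization to keep group sizes balanced within each site". The Discussion acknowledges that sites differ: "Contexts between distinct sites vary, potentially confounding attribution of outcomes to intervention".

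On size, the paragraphs after Table 1 give a "target recruitment of 128 participants, with 64 in each delivery group (videoconference and telephone"). The assumptions behind this target are a standardised effect of 0.5, a 5% significance level and 80% power. No ICC, design effect or dropout allowance is mentioned.

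**The concern.** Members of a CONNECT group share facilitators and take part in group reflection each week. In the pilot, participants reported forming bonds with facilitators and fellow members. Their post-program scores can therefore be positively correlated. A random effect for the person does not absorb an effect shared by everyone in a group. Nor does the crossover cancel it, because a CONNECT group effect arises only after CONNECT and not in the same person's control period.

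Table 1 adds weight to this. Outcomes at T4 are scheduled only for those who receive CONNECT second, so those who receive it first have no post-control score. The randomised contrast then rests largely on week 6, between persons, with about 8 CONNECT groups on one side.

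At stake are confidence intervals that are too narrow and a false-positive rate above the nominal 5%. Site raises a different issue. Balancing allocation within site and then leaving site out of the model keeps explainable variance in the error term, which costs precision.

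**Working it through.** **1. The plan's own figure.** For two independent means with d = 0.5, two-sided alpha 0.05 and power 80%, the t-based formula gives 63.77, so 64 per group and 128 in total. The normal approximation gives 63 per group. Power at 64 per group is 80.1% (t) or 80.7% (normal). A one-sided test needs 51 per group and a paired test 34 in total, so neither gives 128. The target is therefore that of two independent samples without a design effect. The article attaches the 64 to delivery groups; 1:1 allocation to sequence also gives 128/2 = 64 per sequence, which is used below.

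**2. Clusters.** 4 sites × 2 modes × 2 groups = 16 CONNECT groups, and 128/16 = 8 per group. This is the top of the stated 6–8. An even split gives about 8 groups per sequence.

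**3. Formulas.** The design effect is DE = 1 + (m − 1) × ICC. The variance of the difference is multiplied by v = (1 + DE)/2 if only CONNECT is clustered, and by v = DE if both conditions are equally clustered. If clustering is ignored:
- type I error = 2 × [1 − Φ(1.96/√v)]
- power at 64 per sequence, without baseline adjustment = Φ(0.5/√(2v/64) − 1.96)
- total N for the planned power = 128 × v, rounded up

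**4. Results for m = 8.** The ICC values are assumptions.

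| ICC | Clustered | v | Type I error if ignored | Power at 128 | N needed |
|---|---|---|---|---|---|
| 0.01 | CONNECT only | 1.035 | 5.4% | 79.4% | 133 |
| 0.05 | CONNECT only | 1.175 | 7.1% | 74.2% | 151 |
| 0.10 | CONNECT only | 1.35 | 9.2% | 68.2% | 173 |
| 0.01 | both | 1.07 | 5.8% | 78.1% | 137 |
| 0.05 | both | 1.35 | 9.2% | 68.2% | 173 |
| 0.10 | both | 1.70 | 13.3% | 58.3% | 218 |

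Example, ICC 0.05 with CONNECT only clustered: DE = 1 + 7 × 0.05 = 1.35; v = (1 + 1.35)/2 = 1.175; 1.96/√1.175 = 1.81, which gives 7.1%.

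With m = 6 and ICC 0.05, type I error is 6.5% (CONNECT only) or 8.0% (both).

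**5. Simulation check.** The week-6 contrast was simulated with 4 sites of 32 and 6,000 runs per setting, ignoring groups. With only CONNECT clustered, type I error was 6.6% at ICC 0.05 and 9.9% at 0.10. With both clustered it was 9.5% and 13.9%. These agree with the formulas to within about 0.7 percentage points.

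**6. Site.** In the same simulation, with allocation balanced within site and no therapy-group effect, leaving site out gave a type I error of 4.4% at a site ICC of 0.05 and 4.0% at 0.10. Including site brought it back to about 5%.

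**7. Baseline adjustment.** The power figures in step 4 are for unadjusted means, whereas the plan adjusts for baseline. Assume a baseline–outcome correlation r of 0.5 (range 0.4 to 0.6) and the same ICC after adjustment, and multiply v by 1 − r². At m = 8 and ICC 0.05, power before dropout is then 85% (81–90%) with CONNECT only clustered and 80% (76–86%) with both. For r = 0.5 and CONNECT only, v = 1.175 × 0.75 = 0.881.

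**The case against.** The strongest reply is that this is one paragraph of a condensed article. It names a class of model and its purpose but does not set out the random effects. A group random effect and a site term would contradict nothing in it, and an unseen analysis plan may contain both. This stands in part: a reader might infer that the person is the only cluster in the model, and the article does not say so. But the paragraph does list its sources of dependence and its adjustments, and group and site are absent from both lists. The sample size, which an analysis plan cannot change, assumes independence as well.

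A reader might also infer that the two omissions together inflate false positives. They do not. Ignoring groups is anti-conservative, while ignoring site is mildly conservative.

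Other limits stand. The size of the problem depends on an ICC the documents do not give. Groups of 8 are the upper end of the stated range. Equal clustering in the control condition is only a possibility, since the article describes no fixed control groups. A loss of power to 74% or 68% is not established, because baseline adjustment may recover it (step 7). Finally, delivery sequence could mean the order of treatments or the order of telephone and videoconference at a site, so mode order may already be in the model.

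**Conclusion.** The point holds in a limited form. Followed as written, the analysis omits the within-group correlation that a group-delivered program can produce, and the sample size omits it too. For any positive ICC the test is then anti-conservative. The inflation is negligible at ICC 0.01 and material from about 0.05, where type I error is about 7% with CONNECT only clustered and about 9% with both. The upper figure of 13.3% needs ICC 0.10 and equal clustering in the control condition. All of these figures assume groups of 8 and a between-person comparison of 64 with 64.

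The documents do not support a flat statement that the standard errors are wrong: that depends on an unknown ICC and on a random-effects structure the article does not spell out. Omitting site is a separate and smaller matter of lost precision. The change should be made while data collection is still under way, but it does not call the design into question.

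**What to change.** In the planned mixed model:

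- Add a random effect for CONNECT group, partially nested. Control participants form their own clusters unless they attend identifiable groups, in which case the program group is the cluster.
- Add a fixed effect for site (four levels).
- Use Satterthwaite or Kenward-Roger degrees of freedom, because there are only about 16 groups.
- Add delivery mode only if it is not aliased with site or period. Two sites start with videoconference and two with telephone; if that order follows the trial periods, mode at week 6 is determined by site.
- State which sequence the model adjusts for.

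Make sure a coded group ID reaches the analysts. Outcome data are to be labelled by participant code without allocation, so this variable must be supplied deliberately. Nothing in the article says that it is not recorded.

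Restate power at 128 over a stated ICC range. Without baseline adjustment, at ICC 0.05 and groups of 8, it is about 74% if only CONNECT is clustered and 68% if both conditions are. It is higher with baseline adjustment, and the assumed correlation should be given.

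The cost is analysis wording, one coded variable and a short addition to the sample-size paragraph. The downside is somewhat wider intervals and fewer degrees of freedom.
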